## Abstract

**Clinical trial registration:**

[www.ClinicalTrials.gov], identifier [NCT05174871].

## Introduction

The worldwide prevalence of obesity has steadily increased during the last decades (1). Obesity in children is of particular concern, as excessive weight gained during childhood can be tracked into later life: approximately 80% of children with overweight or obesity will stay obese as adults, thereby increasing risk for associated metabolic disorders including type 2 diabetes and cardiovascular disease (2–7). Importantly, improving obesity status during childhood and adolescence is associated with reduced risk for obesity and co-morbidities during adulthood (7). Lifestyle interventions aimed at increasing physical exercise and improving diet quality are the main current obesity therapeutic strategy. However, these interventions have proven challenging to implement at the population level and results are typically insufficient, especially regarding long-term maintenance of the beneficial effects. Therefore, developing more efficient strategies to tackle childhood obesity is a public health imperative.

Time-restricted feeding (TRF) interventions have recently emerged as a promising strategy for weight loss and metabolic health improvements. This strategy consists of restricting the hours for feeding to a specific interval during the day. An increasing number of studies have examined the effects of TRF in adult subjects [for a review of studies see (8)]. These studies are very heterogeneous as they show different (1) length for the TRF (ranging from 4 to 13 h, with a majority of studies between 8 and 10 h); (2) time of day for the restriction (breakfast, lunch, or dinner); (3) duration of the intervention (from 4 days to 16 weeks, being 8–12 weeks the most common time period); and (4) target population (from athletes to adults with obesity) (8). Despite this heterogeneity, the studies generally report significant improvements in BMI, lipid metabolism, and glucose homeostasis (8, 9). However, most interventions targeted adult subjects and there is a lack of data regarding the effects on younger individuals.

The main objective of this clinical study is to evaluate the safety and effectiveness of a TRF intervention in children and adolescents with obesity and determine whether the potential benefits of the intervention are maintained over time (Figure 1). Furthermore, we will explore potential mechanisms mediating TRF effects, specifically focusing on the role of the circadian rhythm and the gut microbiome (Figure 1). For this purpose, we have designed a randomized clinical study in which children and adolescents with ages between 8- and 18-year-old with obesity are subjected to a 2-month TRF intervention and followed-up for 24 months. We will measure anthropometric parameters, adiposity, glucose metabolism, and the lipid profile.

**FIGURE 1 F1:**
[figure not shown]
Summary of the study hypothesis.

## Methods and analysis

### Experimental design and study setting

This is a parallel-group randomized-controlled clinical study performed at the Endocrinology department of Sant Joan de Déu Children’s Hospital, a tertiary care center located in Barcelona (Spain). Recruitment started in January 2022 and is expected to end in December 2022. Candidates undergo the study screening on their regular visits at the hospital and are informed about the study. Whether they agree to participate, parents or legal guardians sign the informed consent, and participants over 12 years of age sign the informed assent document as well. Participants are then randomly assigned to two groups for a 2-month intervention:

- Control group: this is an active control group with the standard obesity treatment protocol at the hospital and no feeding time restrictions.

- TRF group: in addition to the same standard treatment protocol, participants in this group will be subjected to TRF (16 h fast and 8 h feed, 6 days per week).

The study is in accordance with the Helsinki Declaration of 1975 (revised in 2008), has been approved by the local Ethical Committee (ID: PIC-130-219), and was registered at ClinicalTrials.gov (ID: NCT05174871) prior to the start of recruitment.

### Recruitment and eligibility criteria

Participants are recruited from the obesity clinical program at Hospital Sant Joan de Déu based on the eligibility criteria stated below. Approximately 50% of patients with obesity are female so we expect a similar percentage of participants in the study. The study is introduced to the families by the pediatrician and those interested in participating are scheduled for a screening visit at the hospital where they sign the informed and assent consent documents. At the screening visit, 2 weeks before the baseline visit (time 0), participants are provided with an ActTrust 2 actigraph that they wear until the next visit, a fecal sample collection kit, and instructions to fill up a 4-day food registry. At the baseline visit, participants return the actigraph and provide the fecal sample and the food registry.

Participants are selected based on the following criteria:

- Inclusion criteria: age between 8 and 18 years and obesity, defined as BMI-SDS > 2 standard deviations based on World Health Organization growth charts (WHO).

- Exclusion criteria: bariatric surgery; spontaneous TRF for more than 12 h per day; diabetes with insulin treatment; pregnancy; intellectual disability; prescription of drugs for appetite or weight loss (or changes in dose) during the 3 months prior to recruitment.

### Intervention

All participants receive the standard obesity treatment protocol at the Hospital, reported elsewhere (10, 11). This protocol consists of a family-targeted behavioral intervention provided by pediatric endocrinologists and dietitians aimed at implementing healthy dietary habits and increasing physical activity (10, 11). Briefly, dietary recommendations are based on the Mediterranean diet following our local guidelines. We use the Harvard plate method (12) as a tool to improve portion size and balance the meals aiming to reduce overall calorie consumption. Furthermore, we advise participants to limit sedentary activities and screen time, as well as to get active in their daily activities. Finally, we recommend a minimum of 60 min of moderate intensity physical activity per day, according to WHO guidelines.

In addition to the standard protocol, participants randomized into the TRF group have their feeding time restricted to 8 h per day for 6 days per week, with 1 day with no time restrictions. Only water and infusions with no sugar or artificial sweeteners are allowed during the fasting period. To facilitate adherence to the intervention, participants and families are allowed to decide the no-restrictions day as well as the 8-h time interval that best fits their daily schedules; however, this interval is always between 10:00 and 22:00 (for instance, a family can choose 10:00–18:00, while another one can choose 14:00–22:00). Participants use a calendar page to report the days they completely adhere to the intervention (8 h of feeding time), partially adhere (for instance, 10 h instead of 8 h), or did not adhere (12 h or more). A phone call at the third week of intervention and a presential visit at the hospital at week 5 allow for adherence monitoring and improvement. Potential adverse events are evaluated at the 3-week phone call, 5-week, and 2-month visit, and specifically include headache, dizziness, diarrhea, and constipation, as well as any other health-related problem participants might report. Furthermore, a physical medical examination is performed by the pediatrician at the 5-week and 2-month visit. Other parameters considered for safety assessment include anthropometric measurements, hepatic and renal function, glucose and lipid metabolism, and mental health symptoms assessed at all time-points (see section “Outcomes” for details).

### Study visits

To facilitate logistics of the study, participants are organized in groups with one group starting the intervention every month. Thus, the study is being performed with monthly staggered visits with a maximum of 2 overlapping groups during the 2-month intervention. The intervention visits take place at baseline (time 0) and at the end of the intervention (time 1) (Figure 2). Follow-up visits are scheduled at 12 months (time 2) and 24 months (time 3), and will allow for assessing the long-term effects of the intervention (Figure 2).

**FIGURE 2 F2:**
[figure not shown]
Schematic representation of study design.

### Outcomes

Study outcomes are measured at all-time points (0, 2, 12, and 24 months). The change from baseline to each time-point will be evaluated. The study outcomes are the following:

(i) Primary outcome

*Change in BMI-SDS from baseline*. Weight and height are monitored at all-time points with an electronic scale and stadiometer and combined to calculate BMI-SDS based on the WHO growth charts. Participants will wear minimal clothing during the height and weight measurements.

(ii) Secondary outcomes

*Change in metabolic parameters*. A fasting blood test is performed to analyze glucose metabolism parameters (glucose, insulin, HOMA-IR, and HbA1c levels) and the lipid profile (triglycerides as well as total and LDL/HDL-cholesterol). Circulating hepatic markers GGT, ALT, and ASP, which will allow us to estimate the effects of the intervention in the hepatic tissue, are also quantified. Diastolic and systolic blood pressure is also monitored at each visit.

*Change in body composition*. Body composition is assessed by bioimpedance with a Tanita MC-780 BC instrument, available at the Hospital’s Endocrinology department. We are monitoring the absolute amount and percentage of both total body fat and lean mass as well as abdominal fat mass at all-time points.

*Nutritional analysis*. Four-day food registries are used to quantify daily energy intake as well as dietary macro- and micronutrient composition, providing a context for the potential changes induced by the intervention. The nutritionist reviews the registries with the participants and families at each visit to ensure accurate reporting of portion sizes, cooking methods, ingredients, and intake times. The dietary analysis is performed with DIAL software (Alce Ingenierìa, Spain), which provides daily energy consumption, as well as macro- and micro-nutrient intake.

*The children’s depression inventory*. This is a 27-item scale that is used to evaluate depression symptoms in children and adolescents. It evaluates baseline depression and any potential changes induced by the intervention.

*Circadian rhythm and sleep analysis*. Actigraphy is used to accurately monitor circadian rhythm. Participants are instructed to wear an ActTrust 2 actigraph (Condor Instruments, Brazil) for at least 10 days before each visit. The ActTrust 2 is a wearable wrist band specifically designed to make accurate continuous measurements of activity, light, and temperature. The data collected is used to measure sleep and wakefulness patterns as well as parameters directly related to circadian rhythm, including temperature, activity, and ambient light variation. Actigraphy data will be analyzed with the ActStudio^®^ software (Condor Instruments, Brazil). This software transforms the collected data into the parameters that conform rhythmic behavior, as defined by a wave curve. These parameters include amplitude, acrophase, M10 (daily 10 h of maximum activity) and L5 (daily 5 h of minimum activity), as well as interdaily stability and intradaily variability. In addition, participants answer the Sleep Disturbance Scale for Children (SDSC) (13) and Pediatric sleep questionnaire (PSQ) (14) at every visit to screen for sleep quality and potential problems.

*Fecal microbiota analysis*. Bacterial DNA will be isolated from stool samples and microbiota composition will be determined by 16S-sequencing. With this analysis, we will evaluate intervention-induced changes in the intestinal microbiota composition, and assess whether these potential changes are maintained over time.

### Sample size

With no data on TRF interventions in subjects within our age range, an exact calculation of sample size is not feasible. To estimate sample size, we relayed on our data from more than 150 patients with obesity (8–18 years of age) at the Hospital’s Endocrinology department that have undergone the standard obesity treatment protocol. This group would be equivalent to the Control group. The standard deviation of BMI-SDS change over a period of 2 months during a lifestyle intervention was 0.35 units. Based on these data, with type I error of 0.05 and power set at 80%, we will need 64 subjects to detect a difference of 0.25 units in BMI-SDS change between groups. To account for a potential high drop-out rate, we aim to recruit a total of 80 subjects, anticipating up to a 20% participant loss.

### Randomization

Participants are randomly allocated into Control and TRF groups with an allocation ratio of 1:1. Randomization is performed in blocks (block size of 4) stratifying by gender and age (younger/older than 12 years of age) to allow for a balanced number of participants in each group. Randomization lists were obtained from computer-generated sequences. Participant randomization is implemented in REDCap (Research Electronic Data Capture).

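### A single, published block size of 4 in a one-department trial whose arms cannot be masked lets anyone tracking a stratum foresee about a third of allocations

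*Protocol article*

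**What the plan says.** The Randomization section of the protocol article gives the whole scheme. The two arms receive equal numbers (1:1), and the blocking rule reads: "Randomization is performed in blocks (block size of 4) stratifying by gender and age (younger/older than 12 years of age". Two genders by two age bands make four strata. The lists are computer-generated, and "Participant randomization is implemented in REDCap (Research Electronic Data Capture".

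Three other parts of the article bear on the point:

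- Setting (Experimental design and study setting): "This is a parallel-group randomized-controlled clinical study performed at the Endocrinology department of Sant Joan de Déu Children’s Hospital". Under Recruitment and eligibility criteria, the pediatrician introduces the study to families within the hospital's own obesity program.
- Masking: the article does not mention it. Under Intervention, in the TRF arm "participants and families are allowed to decide the no-restrictions day as well as the 8-h time interval", and these families also keep an adherence calendar. Controls have no restriction on feeding times.
- Timing: after describing consent, Experimental design and study setting continues "Participants are then randomly assigned to two groups for a 2-month intervention". Recruitment and eligibility criteria has consent signed at the screening visit, and says "At the screening visit, 2 weeks before the baseline visit (time 0), participants are provided with an ActTrust 2 actigraph". No section names the visit at which allocation is released.

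**The concern.** With permuted blocks of one known size, the end of each block follows from its beginning. Hiding the list does not help once past assignments can be seen. Here families and treating staff necessarily know the arm, and one department handles recruitment, treatment and follow-up, so past assignments are plausibly visible to the people who approach the next family.

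A clinician who foresees the next arm can, deliberately or not, bring forward or delay a family, or present the study more or less warmly. Family motivation plausibly drives both adherence and BMI-SDS change. It is not among the adjustment variables named under Data management and analysis (gender, age, baseline BMI-SDS, pubertal status). Measuring weight and height by instrument does not protect against this, because the bias lies in who enters each arm and not in how the outcome is read.

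**Working it through.** The article gives no figure for predictability, so there is none to reproduce.

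**Inputs.** Block size 4, ratio 1:1 and four strata (Randomization); 80 participants to be recruited (Sample size). Assuming equal strata, 80 / 4 = 20 per stratum, or five complete blocks.

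**Certain allocations.** A 1:1 block of 4 has 4! / (2! × 2!) = 6 equally likely sequences. A place is certain once one arm has filled its two places.

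- Places 1 and 2: never certain.
- Place 3: certain if the first two went to the same arm, 2 of 6 sequences = 1/3.
- Place 4: always certain.

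Expected certain places per block = 1/3 + 1 = 4/3. Share = (4/3) / 4 = 33.3%, and 80 × 1/3 = 26.7, about 27 participants.

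If the last block is incomplete the share is slightly lower. With 18 in a stratum: 4 × (4/3) / 18 = 29.6%. With 21: 5 × (4/3) / 21 = 31.7%. Over 17 to 22 per stratum the range is about 30% to 33%.

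**Best guessing.** The rule is to guess the arm that is behind and toss a coin when the arms are level. The probability of a correct guess is:

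- Place 1: 1/2.
- Place 2: 2/3.
- Place 3: (1/3) × 1 + (2/3) × (1/2) = 2/3.
- Place 4: 1.

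Sum = 17/6 = 2.833 of 4, so 17/24 = 70.8%.

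**Varying block sizes.** The alternatives were simulated with 5,000 strata of 20 participants each. Sizes were drawn with equal probability, and the observer was assumed to know the set of sizes but not their order.

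| Block sizes | Certain in advance | Best guess correct |
|---|---|---|
| 4 only (as planned) | 33% | 71% |
| 2, 4, 6 | 4% | 70% |
| 4, 6 | 6% | 69% |
| 4, 6, 8 | 2% | 67% |

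Varying the sizes removes nearly all certainty but only a little of the guessing advantage. Including blocks of 2 leaves guessing almost where it is, because a block of 2 alone is guessable 75% of the time: (1/2 + 1) / 2.

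**The case against.** **The figures need a tracking observer.** One third and 70.8% hold for someone who knows the block size and every earlier allocation in the stratum. The article does not say who sees past allocations. Participants also start in monthly groups. With even accrual over the planned 12 months, 80 / (12 × 4) = 1.7 participants enter a stratum each month. If allocation is released at the baseline visit, two weeks after screening, some earlier enrollees may still be unallocated when the next family is approached, which weakens prediction at that moment. This objection stands as a limit on size: the figures describe the most such an observer could gain, not what will happen.

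**Small blocks have a purpose.** With about 20 per stratum, blocks of 4 give close balance, which is the stated aim. That is fair, but slightly larger varying blocks give up little of it.

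**Masking is not mentioned.** That the trial is open is inferred from the intervention. For families and treating staff no other reading is realistic. Nothing is claimed here about outcome assessors.

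**A stronger reading of the timing.** A reader might join the two sections on consent and infer that assignment comes directly after consent, before the two-week run-in, so that baseline actigraphy, food registry and stool sample already reflect the arm. The documents do not support this. The word *then* gives order only, the sentence ties assignment to the intervention, allocation at time 0 fits equally well, and the design figure is not shown. Nor does the article say that the food registry decides the exclusion for spontaneous TRF, so it cannot be concluded that allocation precedes that eligibility check. Weight and height for the primary outcome are measured at time 0, not during the run-in. What remains is an ambiguity to clear up.

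**Conclusion.** The point holds for the block scheme. The article itself fixes and publishes one block size of 4, in a setting where arms cannot be masked and one department runs the trial. A person tracking a stratum would know about one third of allocations beforehand (30% to 33% when last blocks are incomplete; about 27 of 80 when all are complete) and guess 70.8% correctly.

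This rests on three assumptions: knowledge of the block size, sight of past allocations within the stratum, and roughly equal strata. The documents give no basis for converting predictability into a bias in BMI-SDS, so none is claimed. It is an avoidable weakness with a cheap remedy, not a flaw that invalidates the trial. On timing, the only supportable conclusion is that the visit of allocation is unstated in the article.

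**What to change.** - For allocations still to be made, replace the fixed block of 4 with randomly varying sizes such as 4, 6 and 8 within the same four strata, and do not disclose the sizes to recruiting staff. Cost: a new randomization table, and a possible imbalance within a stratum of up to 4 instead of 2. Some predictability remains, with best guessing at about 67%.
- The article expects recruitment to end in December 2022. If it is complete, the scheme cannot be changed; report instead who could see the block size and past allocations when families were approached.
- Reconcile Experimental design and study setting with Recruitment and eligibility criteria in one sentence stating that allocation is released at the baseline visit, after eligibility is confirmed and the run-in data are collected. If practice was different, state what was done. This costs nothing beyond the sentence.

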### Data management and analysis

Study data are collected, managed, and stored using REDCap tools hosted at Hospital Sant Joan de Déu (15, 16). REDCap is a secure, web-based software platform designed to support data capture for research studies. To assess the comparability of the two groups, continuous variables will be compared using Student’s *t*-test or non-parametric tests for those with a non-normal distribution. Categorical variables will be assessed with the Chi-square test. Multivariate linear and logistic regression models will be used to analyze the effects of the TRF intervention in comparison with the Control group. These methods will allow for adjustment by potential confounding variables, including gender, age, baseline BMI-SDS, and pubertal status. Furthermore, the design of the study allows for secondary analyses. Specifically, we will carefully examine whether (1) gender; and (2) pubertal status are determinants of the short- and long-term TRF-induced effects by analyzing the different data subsets. Statistical calculations will be performed in JMP v16 software (SAS Institute Inc., Cary, NC).

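### No continuous secondary outcome has its own baseline value named as a covariate; the only baseline outcome value named is BMI-SDS

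*Protocol article*

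**What the plan says.** The Outcomes section states for the study outcomes as a whole: "The change from baseline to each time-point will be evaluated". The primary outcome is "Change in BMI-SDS from baseline". The secondary outcomes include fasting blood measures, for example "A fasting blood test is performed to analyze glucose metabolism parameters (glucose, insulin, HOMA-IR, and HbA1c levels", together with lipids, liver enzymes, blood pressure, bioimpedance measures, a depression score, and sleep and actigraphy parameters. All are measured at baseline and at every later visit.

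The Data management and analysis section gives a single model description: "Multivariate linear and logistic regression models will be used to analyze the effects of the TRF intervention in comparison with the Control group". On covariates it adds: "These methods will allow for adjustment by potential confounding variables, including gender, age, baseline BMI-SDS, and pubertal status". The same section plans significance tests of group comparability: "To assess the comparability of the two groups, continuous variables will be compared using Student’s *t*-test or non-parametric tests", and "Categorical variables will be assessed with the Chi-square test".

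The Randomization section stratifies by gender and by age below or above 12 years. Both factors are therefore among the named covariates.

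**The concern.** Of the four named covariates, only baseline BMI-SDS is the starting value of an outcome, and that outcome is the primary one. A secondary outcome such as ALT, HOMA-IR or systolic pressure, modelled as change with only these four terms, is not adjusted for where the participant started on that measure.

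A change score is in general negatively correlated with its own baseline, because high starters tend to fall and low starters tend to rise. Leaving the baseline out has two effects. Residual variance that the collected data could remove stays in the comparison. And if one arm happens to start higher on the measure, regression to the mean makes that arm appear to fall more.

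The secondary outcomes carry weight here. The Intervention section counts hepatic function, glucose and lipid metabolism, and mental health symptoms among the safety parameters, and safety is part of the main objective. A chance difference in starting ALT or depression score could create or hide an apparent difference between the arms.

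**Working it through.** **The plan's own figure.** Inputs from the Sample size section: SD of the 2-month change in BMI-SDS 0.35, difference 0.25, type I error 0.05 (taken as two-sided), power 80%.

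- Normal approximation: n per arm = 2 × (1.960 + 0.842)² × 0.35² / 0.25² = 30.8, so 31 per arm and 62 in total.
- Noncentral t: power is 0.790 at 31 per arm and 0.803 at 32 per arm, so 64 in total.
- Drop-out: 64 / (1 − 0.20) = 80.

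The stated 64 and 80 reproduce. They concern the primary outcome, whose own baseline is already named, so nothing below changes them.

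**Precision for a secondary outcome.** Let s be the SD at both visits (assumed equal) and rho the correlation between baseline and follow-up (not in the document; assumed 0.3 to 0.9).

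- Variance of the unadjusted change: 2s²(1 − rho)
- Residual variance after own-baseline adjustment: s²(1 − rho²)
- Ratio, adjusted to unadjusted: (1 + rho)/2
- Reduction in standard error: 1 − √[(1 + rho)/2]
- Power of a contrast that has 80% on the unadjusted change: Φ(2.802/√ratio − 1.960)
- Evaluable number giving the precision that 64 give unadjusted: 64 × ratio, rounded up

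**Shift from a chance imbalance.** If the TRF arm starts higher by d, the unadjusted change-score contrast moves by −(1 − rho)d. With 32 evaluable per arm, the standard error of a chance baseline difference is √(2/32) = 0.25 SD. The last column uses a difference of that size.

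| rho (assumed) | Variance ratio | SE reduction | Power | Equivalent N | Size of shift for d = 0.25 SD |
|---|---|---|---|---|---|
| 0.3 | 0.65 | 19.4% | 93.5% | 42 | 0.175 SD |
| 0.5 | 0.75 | 13.4% | 89.9% | 48 | 0.125 SD |
| 0.7 | 0.85 | 7.8% | 86.0% | 55 | 0.075 SD |
| 0.9 | 0.95 | 2.5% | 82.0% | 61 | 0.025 SD |

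Seen from the other side, the unadjusted standard error is 1/√ratio times the adjusted one: 1/√0.65 = 1.24 at rho 0.3 and 1/√0.95 = 1.03 at rho 0.9.

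**What the table compares.** The formulas set two models side by side that hold no other covariates. With the four named covariates in both, the relevant SDs and rho are those left after them. Where these covariates already predict the change, part of the gain has been taken and the remainder is smaller. The figures are therefore best read as up to, and not as a forecast.

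**Change or follow-up as response.** If Y1 − Y0 = a + b·arm + c·Y0, then Y1 = a + b·arm + (c + 1)·Y0. The arm effect b is the same, so own-baseline adjustment is fully compatible with reporting change.

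**The case against.** The strongest reply is that the covariate list is illustrative. It is introduced as including four items, and nothing rules out more. A condensed article may leave covariates for each outcome to an analysis plan that is not shown. This stands: a reader might infer that own-baseline adjustment has been decided against, and the text does not say so. What remains is that the one description given covers all outcomes, and the one baseline outcome value it names serves only the primary. Followed as written, the secondary models lack their own baseline.

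A reader might also infer that the comparability tests decide which covariates enter the models. No sentence links the two, and the four covariates are named without reference to any test result. Under randomisation such p-values answer no useful question, but reporting them changes no treatment estimate and costs no precision.

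A third tempting reading is that the secondary results are biased. They are not, on average: randomisation removes that. The shift shown is conditional on the imbalance that happens to occur, and a change score already removes part of the baseline difference, leaving only the fraction 1 − rho.

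Finally, the size rests on an assumed rho. At 0.9 the gain is only 2.5% of the standard error. This also stands, and it is why a range is given.

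**Conclusion.** The point holds in a limited form, for continuous secondary outcomes only. Applied as written, the named covariates leave these outcomes without adjustment for their own starting value. Adding it would lower the standard error by up to about 19% at rho 0.3 and about 2.5% at rho 0.9, and would remove the conditional shift from a chance baseline difference. These figures assume equal SDs at the two visits and a rho that the document does not give.

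The primary analysis, its covariates and the sample size of 64 evaluable and 80 recruited are sound on this point. Microbiota composition is not a single continuous outcome and lies outside it. The matter is one of efficiency and of fixing the model in advance, and it is modest in weight.

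**What to change.** State in the analysis section that, for each continuous secondary outcome, the follow-up value or the change is regressed on arm, the baseline value of that same outcome, and the four covariates already named (age, gender, pubertal status and baseline BMI-SDS). State also that this list is fixed in advance and used whatever balance is observed.

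The cost is one more covariate, so one degree of freedom, per model. The baselines are already collected at time 0, so no visit, measurement or sample size changes.

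As an optional tidy-up, describe baseline characteristics by arm without significance tests. This would improve the report but would not alter any effect estimate.
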